### Cancer Treatment Delivery

Cancer treatment delivery metrics include treatment satisfaction, number of treatment breaks, and number of changes in regimen. Cumulative numbers of treatment breaks and changes in regimen over the follow-up time frame will be summarized across treatment arms and compared using the Poisson regression approach described above for healthcare utilization outcomes.

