#### INCLUSION CRITERIA:

##### 1. Curative Intent Group:

- ≥ 18 years of age;
- medical chart confirmed diagnosis of a solid or hematological malignancy within the last 10 years;
- had an appointment at a participating site with a participating oncologist in the last year;
- willingness to be randomized (post-implementation only);
- have initiated primary treatment with curative intent within the past 3 months (i.e., as patients receive surgery, standard- or high-dose chemotherapy, biological therapy, and/or radiotherapy);

- provider confirmed planned treatment and follow-up within the Northwestern Medicine hospital and clinics;
  - provider confirmed planned treatment and follow-up within the Northwestern Medicine hospital and clinics; and
  - able to read English or Spanish.
2. Non-Curative/Palliative Intent Group:
- ≥ 18 years of age;
  - medical chart confirmed diagnosis of advanced or metastatic solid or hematological malignancy within the last 10 years;
  - had an appointment at a participating site with a participating oncologist in the last year
  - provider confirmed planned treatment and follow-up within the Northwestern Medicine hospital and clinics;
  - willingness to be randomized (post-implementation only);
  - undergoing cancer treatment with non-curative/palliative intent (e.g., patients with advanced or metastatic disease who receive chemotherapy, biological therapy, and/or radiotherapy to control or slow advance of their disease);
  - provider confirmed planned treatment and follow-up within the Northwestern Medicine hospital and clinics; and
  - able to read English or Spanish.
3. Cancer Survivorship Group:
- ≥ 18 years of age;
  - medical chart confirmed diagnosis of solid or hematological malignancy within the past 10 years;
  - had an appointment at a participating site with a participating oncologist in the last year;
  - provider confirmed planned treatment and follow-up within the Northwestern Medicine hospital and clinics;
  - willingness to be randomized (post-implementation only);
  - completed active cancer treatment with curative intent, including those who may be receiving maintenance or prophylactic cancer treatment;
  - provider confirmed planned cancer follow-up care (with or without treatment) within the Northwestern Medicine hospital and clinics; and
  - able to read English or Spanish.

### Aim 3

- *Clinician Focus Groups*

- Clinical or operational leader in an NM clinic participating in cPRO implementation

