| Diagnoses              | All diagnoses on problem list/encounter diagnoses                                             | Encounter ID, diagnosis date, provider ID, diagnosis code, diagnosis code system,                                                                                  |
| Procedures             | All procedures in EHR                                                                         | Encounter ID, procedure date, provider ID, procedure code, procedure code system,                                                                                  |
| Cancer Medication      | All cancer meds from beacon treatment plan                                                    | Medication code, start/end date, dose, route of administration, treatment intent                                                                                   |
| Symptomatic Medication | All medication listed in EHR                                                                  | Medication code, start/end date, dose, route of administration                                                                                                     |
| Vital Signs            | BMI, multiple rows per patient                                                                | BMI, measure date                                                                                                                                                  |
| PROMIS measures        | All cPRO completions                                                                          | cPRO date completed, scores for 5 domains                                                                                                                          |
| REDCap study data      | All surveys in REDCap                                                                         |                                                                                                                                                                    |
| Study specific fields  | Indicators for if Pre/Post I, randomized arm, site, cancer continuum, one row per participant |                                                                                                                                                                    |

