## 5.0 STUDY HYPOTHESES

The primary implementation hypothesis is that the system-level multicomponent package of implementation strategies for oncology symptom assessment and management at NMHC will increase the cluster-level reach rate of cPRO to eligible patients. The primary effectiveness hypothesis is that cancer patients at NMHC who are randomized to EC will have better PRO outcomes over time compared to cancer patients at NMHC who are randomized to UC.

Secondary implementation hypotheses are that the system-level multicomponent package of implementation strategies for oncology symptom assessment and management at NMHC will increase adoption of cPRO at the provider level as evidenced by referrals for appropriate services when a patient triggers in cPRO and the reach rate of patients enrolling in the portal. It is also hypothesized that system-level strategies will be appropriate, acceptable, feasible, and sustainable. Secondary effectiveness hypotheses are that cancer patients at NMHC who are randomized to EC will have lower healthcare utilization, better cancer treatment delivery, better cancer treatment satisfaction, better health related quality of life, better self-management, lower toxicity, better physical health and lower financial burden compared to cancer patients at NMHC who are randomized to UC.

The exploratory hypothesis is that cancer patients randomized to EC will have better clinical outcomes compared to cancer patients randomized to UC.

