## 6.0 SAMPLE SIZE CONSIDERATIONS

### Implementation

It is anticipated that data gathered through the electronic health record will be available for approximately 12,000 patients to be used for the implementation analyses. This estimate is based on the sizes of the clusters of clinics that are involved in the NU IMPACT study. Based upon prior years' metrics, an annual volume of over 18,000 unique patients across the clinics is projected, ranging from 1,500-4,500 per cluster. We will study implementation of cPRO for all adult patients being treated in all three phases of the cancer treatment continuum. Although there is some cross-cluster variability in proportion of patients in each treatment phase, we estimate that on average each cluster will see 30% of its new patients being treated for cure, 30% will be treated for life extension, and 40% will be disease-free survivors. Based upon our prior experience with similar studies, we anticipate that approximately 2/3 of patients will meet the inclusion criteria listed above, hence the total anticipated 12,000.

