## 9.2 Secondary Outcomes – Effectiveness

### Healthcare Utilization

Healthcare utilization metrics include the numbers of ER/urgent care visits, hospital admissions and days of stay, unscheduled visits, and supportive care visits for all three curative, non-curative and survivorship groups across the follow-up time frame for each individual. These data will be captured through the electronic medical record for within-NMHC utilization and by data collection directly from patients for outside-NMHC utilization at baseline, 6 and 12 months. Individual variables will be summarized across treatment groups using means and five-number summaries (minimum, 25th percentile, median, 75th percentile, maximum). For formal statistical analysis, we intend to create a global summary score of healthcare utilization by summing the counts of all variables listed above. Poisson regression will be used to compare the global healthcare utilization summary measures at 6- and 12-month time points across treatment arms in separate analyses for each time point. Primary analyses will compare Post-I EC v. Post-I UC as the primary predictor of interest with model adjustments for cluster, cancer continuum, gender, language preference, and time of enrollment. To evaluate potential contamination effects as described above, differences across the Post-I EC, Post-I UC and Pre-I groups will also be jointly evaluated. Overdispersion will also be evaluated, and if present, will be addressed through the use of quasi-Poisson modeling to account for additional variance.

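### Treatment breaks and regimen changes are compared without limiting the analysis to participants who have a regimen, so the quasi-Poisson standard error may be too small, and no favourable direction is stated for regimen changes

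*Combined protocol and SAP*

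**What the plan says.** SAP 9.2, Cancer Treatment Delivery, gives the analysis in one sentence: "Cumulative numbers of treatment breaks and changes in regimen over the follow-up time frame will be summarized across treatment arms and compared". The method is carried over: the counts are "compared using the Poisson regression approach described above for healthcare utilization outcomes".

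The carried-over model, in SAP 9.2, Healthcare Utilization, is specified "for all three curative, non-curative and survivorship groups". It is fitted "with model adjustments for cluster, cancer continuum, gender, language preference, and time of enrollment", and moves to quasi-Poisson if overdispersion is found. The treatment-delivery paragraph adds no restriction to participants on treatment.

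Protocol 3.0 admits to the survivorship group patients who have "completed active cancer treatment with curative intent, including those who may be receiving maintenance or prophylactic cancer treatment". SAP 6.0 expects that, among new patients, "40% will be disease-free survivors"; Protocol 4.0 puts the same share at 30%.

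SAP 5.0 hypothesises "better cancer treatment delivery" under enhanced care. SAP 2.0 lists the two counts without defining a break or a change, naming the participants at risk, or saying whether more or fewer is favourable.

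**The concern.** Utilisation makes sense in everyone, because anyone can visit an emergency room. A treatment break can occur only in someone with a treatment to interrupt. Using the all-groups model for these counts brings in survivors without a regimen, who cannot have an event.

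This has two consequences. First, the standard error may be too small. Cancer continuum is a covariate, so a stratum at or near zero contributes almost nothing to the estimated rate ratio. It still enters the single dispersion factor that scales the standard error, and can pull it down, so that a chance difference is called significant too often. Second, and separately, a regimen change could reflect a planned sequence, progression or toxicity. Without a stated direction, a difference in that count does not readily support or contradict the hypothesis.

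**Working it through.** **Inputs from the documents.** About 1,000 randomised 1:1 (SAP 3.0, 6.0); survivor share f = 0.30 (Protocol 4.0) or 0.40 (SAP 6.0), applied here to the randomised sample. The size reproduces for the PROMIS outcomes with 12 measurements: 2 × (2.576 + 1.282)² × [(1 + 11 × 0.5)/12] / 0.3² = 179.1, so 180 per arm, 360 in total, and 360/(1 − 0.64) = 1,000. The SAP states no figure for the two counts.

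**Assumed, because the documents are silent.** Two-sided 5% test; a mean of 0.8 events per treated patient per year (1.04 in the non-curative group); dispersion φ of 1 to 3 among treated patients.

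**Mechanism at the extreme.** If all survivors have zero events, they add a fraction f of the residual degrees of freedom and no Pearson residual. The estimated dispersion is then about (1 − f)φ, and the standard error shrinks by a factor √(1 − f): 0.837 at f = 0.30 (16% too small) and 0.775 at f = 0.40 (23% too small). The type I error is 2[1 − Φ(1.96 √(φ_used/φ))]:
- f = 0.30: 1.96 × 0.837 = 1.640, giving 10.1%.
- f = 0.40: 1.96 × 0.775 = 1.518, giving 12.9%.
- f = 0.40 and φ = 1.5: 0.6 × 1.5 = 0.9, so plain Poisson is used (φ_used = 1); 1.96 × √(1/1.5) = 1.600, giving 11.0%.
- φ = 1: plain Poisson is correct, giving 5%.

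**Simulation of the planned model.** N = 1,000, adjusting for cluster, continuum, gender, language and quarter, with quasi-Poisson when the Pearson dispersion exceeds 1:

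| Assumption | Rejection under no effect |
|---|---|
| All survivors zero, treated φ 1.5 to 3, f = 0.30 | 10.3% to 11.3% |
| Same, f = 0.40 | 11.1% to 14.8% |
| All survivors zero, treated counts Poisson | 5.4% to 6.0% |
| 2% to 50% of survivors with events at the treated-patient rate | 2.8% to 5.4% |
| Every survivor at 0.05 per year, same φ as treated patients | 5.0% |
| Every survivor at 0.05 per year, negative binomial variance | 7.5% to 8.6% |

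A simpler model (arm and continuum only; gamma-Poisson counts, shape 0.5, mean 1 in treated patients) fills in the case closest to the eligibility text. With 30% to 50% of survivors on maintenance at a low rate (0.1 to 0.2 per year), it rejects about 6% to 10%. With 2% of survivors at the full treated-patient rate, it rejects 5.5% to 6.1%. Simulation error with 1,500 trials is √(0.05 × 0.95/1500) = 0.56 percentage points, so values between about 4% and 6% cannot be told from nominal.

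**The same check after a change.** Restricting to participants with a regimen gives 4.4% to 6.5% with the full covariate set. If survivors on low-rate maintenance stay in that set and the pooled dispersion is kept, the range is about 5% to 8%. Sandwich standard errors give 4.0% to 6.2% with the full covariate set, and about 5% to 7% when the low-rate cases are included.

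**The case against.** A reader might infer that survivors have zero counts by construction and that the test therefore runs at about twice its nominal level. The documents do not support this. Protocol 3.0 includes survivors on maintenance or prophylactic treatment, who have a regimen that can be paused or changed. If as few as 2% of survivors have events at the treated-patient rate, or if treated counts are not overdispersed, the error is about nominal. Every rate behind the inflated figures is assumed. This objection stands against any single figure. It does not remove the low-rate maintenance case, which stays above nominal, and the quasi-Poisson step is no safeguard, because the dilution occurs there. Randomisation stratified by continuum protects the estimate from bias, but not its standard error.

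A reader might also infer that the missing direction inflates type I error, or that the plan cannot show better delivery at all. Neither follows. Direction bears only on interpretation, fewer treatment breaks has a natural reading, and SAP 9.2 also lists treatment satisfaction as a delivery metric.

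Nor do the documents show that reasons for a regimen change are unobtainable. The Protocol 19.0 entry, "Medication code, start/end date, dose, route of administration, treatment intent", is a list of field examples for the dataset shared with the Consortium, not the SAP's extraction specification. Making regimen changes purely descriptive is therefore a preference rather than a necessity.

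Finally, robust standard errors alone roughly restore the error rate with everyone kept in. That is correct. The case for restricting the population rests mainly on what the outcome means.

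**Conclusion.** The concern holds as a gap in specification with a possible, unquantified effect on type I error. The two counts have no stated at-risk population, and the pooled dispersion can be too small when many participants are at or near zero. The rejection rate of the nominal 5% test lies between about 5% and about 15%:
- about 5% if treated counts are not overdispersed, or if a few percent of survivors have events at the treated-patient rate;
- about 6% to 10% if some survivors are on maintenance with a low event rate;
- about 10% to 15% if all survivors are at zero and treated counts are overdispersed.

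Which case applies depends on rates the documents do not give. Separately, a difference in regimen changes alone is hard to read against the stated hypothesis. These are secondary outcomes, so the point is worth correcting but does not touch the primary PROMIS comparison.

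**What to change.** In SAP 9.2, Cancer Treatment Delivery:
- Define a treatment break and a regimen change.
- Analyse both counts in participants with an active treatment plan in the EHR at randomisation, including survivors on maintenance. Fixing status at randomisation avoids selecting on later events. Protocol 19.0, Table 3 already names a treatment-plan source for cancer medication.
- Use robust (sandwich) standard errors in place of the single pooled dispersion. This is still needed after the restriction, because survivors on low-rate maintenance remain in the set.
- State that fewer breaks is favourable, and say how regimen changes will be interpreted, for example by treatment intent.
- Reconcile the 30% and 40% survivor shares in Protocol 4.0 and SAP 6.0.

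Healthcare utilisation stays in all three groups. The change is about one paragraph, and SAP 1.0 says SAP modifications need no protocol amendment. The price is a slightly smaller analysis set that omits regimens started after randomisation.

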### Cancer Treatment Delivery Satisfaction, Health Related Quality of Life, Self-Management, Symptoms and Toxicities, Physical Activity, Financial Burden

All of these additional secondary effectiveness outcomes will be measured using the PRO measures described above over regular intervals for each cohort. The analytic methodology described above for PRO data analysis will be applied here.

### Support and Isolation

Social support and isolation metrics will be evaluated as potential mediators of treatment effects on primary outcome PROs. Structural equation modeling of potential mediation effects on the longitudinal PRO outcomes will be implemented using functionality in the lavaan R package.

## 9.3 Exploratory Objectives

Heterogeneity of cancer diagnoses for patients in the NU IMPACT trial makes formal analysis of clinical outcomes a challenge. However, we will undertake exploratory analyses of clinical outcomes to assess differences in the Pre-I, Post-I UC and Post-I EC arms. Clinical endpoints to be ascertained via the electronic medical record through 12 months of follow-up include the following for each cancer continuum cluster: curative intent – recurrence, secondary cancers, disease-free and overall survival; non-curative intent – secondary cancers, progression-free and overall survival; survivorship – recurrence. Kaplan-Meier curves will be used to estimate distributions for time-to-event outcomes disease-free, progression-free and overall survival within treatment arm, and global differences across arms will be compared using logrank tests. Cox proportional hazards regression models will be used to estimate hazard ratios, treating the Pre-I cohort as the referent. Frequencies of binary outcomes recurrence and secondary cancers will be summarized across treatment arms

and compared using chi-square tests. Logistic regression models will be used to estimate odds ratios, treating the UC cohort as the referent with global and pairwise comparisons for Post-I EC v. Post-I UC and Pre-I v. Post-I UC. Regression models will be adjusted for cluster, cancer continuum, gender, language preference, and time of enrollment. If differences in demographic or baseline variables are detected across treatment arms, we will evaluate sensitivity of estimated hazard and odds ratios to further adjustment for these variables. Importantly, given the heterogeneity of outcome rates for different cancers, we will conduct these analyses separately for each type of cancer diagnosis. Given the subset nature of these investigations, these analyses will be considered exploratory.

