## Effectiveness Study

A schematic of the study design that illustrates the effectiveness investigation is depicted in Figure 2. For the last 6 months of each cluster's pre-I phase, eligible participants are invited to consent to monthly administration of a collection of PRO surveys administered through REDCap for one year following consent. One set of comprehensive PRO surveys will be administered at baseline and monthly thereafter, and an additional set of questionnaires will be included with these PRO surveys on a quarterly basis (see Section 2.0 for primary and secondary effectiveness PROs and timing). During post-I, EC becomes available using a 1:1 randomization scheme (EC:UC) to new, consenting patients, but not those in the consented group from the pre-I period who are continuing their care. Randomization will be stratified by cluster, cancer continuum (curative, non-curative, survivorship), gender and language preference. Participants who consent to randomization during post-I will receive the REDCap PRO surveys on the same schedule as those who consented during the pre-I phase. The monthly PRO data collected over one year of follow-up during the post-I embedded patient-randomized trial will be the primary data source for the effectiveness analysis. Additionally, we will compare the post-I EC and UC arms to patients enrolled during pre-I. Pre-I patients will have access to identical tools as UC patients, and the comparison of these arms will be critical for noting potential contamination in provider care subsequent to system-wide implementation strategies.

| Clinical Cluster | Implementation Phase | Y3                         |                            |                              |                              | Y4                                                    |                                                       |                                                       |                                                       | Y5                                                    |                                                       |                                                       |    | Y6 |    |    |    |

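### SAP 9.3 tests overall survival, recurrence and secondary cancers with unstratified log-rank and chi-square tests, although cancer continuum is a randomisation stratum; some power is lost, and the global test is exposed to the Pre-I case mix (minor)

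*Combined protocol and SAP*

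**What the plan says.** SAP 9.3 sets out to "assess differences in the Pre-I, Post-I UC and Post-I EC arms", so two randomised arms and one non-randomised cohort enter together. For the time-to-event endpoints, "global differences across arms will be compared using logrank tests". Frequencies of recurrence and secondary cancers are summarised "and compared using chi-square tests". Neither test is described as stratified.

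The surrounding text bears on how to read this:

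- SAP 3.0, Effectiveness Study: "Randomization will be stratified by cluster, cancer continuum (curative, non-curative, survivorship), gender and language preference".
- SAP 9.3: "Regression models will be adjusted for cluster, cancer continuum, gender, language preference, and time of enrollment". The Cox models estimate hazard ratios with Pre-I as referent. The logistic models take UC as referent and include global and pairwise comparisons.
- SAP 9.3: the endpoints "through 12 months of follow-up include the following for each cancer continuum cluster". As listed there, overall survival and secondary cancers belong to the curative and non-curative groups, recurrence to the curative and survivorship groups, disease-free survival to the curative group only, and progression-free survival to the non-curative group only.
- SAP 9.3: "we will conduct these analyses separately for each type of cancer diagnosis", and "these analyses will be considered exploratory".

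**The concern.** A continuum term in a model does nothing if each analysis is confined to one continuum group. Adjusting for it therefore implies that overall survival, secondary cancers and recurrence are pooled over two groups each, although SAP 9.3 never says so outright. If event rates differ between the pooled groups, an unstratified test counts that difference as unexplained variation. It then gives away power that a stratified test would keep. Where randomisation has balanced the groups, its true error rate also falls below the nominal one.

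For survival the log-rank is the only test named, so the p-value would be unadjusted while the hazard ratio beside it is adjusted. For the binary endpoints two tests are available, the chi-square and the adjusted logistic comparisons, and the SAP does not say which governs.

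The global test has a further exposure. Nothing in the design fixes the continuum mix of Pre-I to that of the randomised arms. SAP 7.2 expects comparability. However, willingness to be randomised is required only post-implementation (protocol 3.0), targeted in-person recruitment was added only post-implementation (protocol 10.0), and Pre-I participants cannot be randomised later (SAP 2.0).

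**Working it through.** **The plan's own figure.** The only effectiveness sample size is for the PROs (SAP 6.0). With 12 monthly measurements and correlation 0.5, the variance factor is (1 + 11 × 0.5)/12 = 0.5417. At two-sided alpha 0.01 and 90% power, n per arm = 2 × (2.576 + 1.282)² / 0.3² × 0.5417 = 330.65 × 0.5417 = 179.1, rounded up to 180. That is 360 in total, and 360/(1 − 0.64) = 1000. The figure reproduces but does not bear on this point: no events, alpha, power or effect size is given for the clinical endpoints.

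**Inputs from the documents.** Allocation is 1:1. The curative/non-curative/survivor mix is 30/30/40 (SAP 6.0) or 40/30/30 (protocol 4.0), so the non-curative share of those two groups is 30/60 = 50% or 30/70 = 43%. Follow-up is 12 months.

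**Assumptions, because the documents give none.** Event rates by continuum, hazard ratio 0.60 (odds ratio 0.5 for recurrence), Pre-I the same size as each arm, size of the Pre-I shift, two-sided 5% tests, exponential times, no censoring before 12 months. All results are simulated.

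**Step 1. Overall survival, EC v. UC, 150 curative + 150 non-curative per arm, balanced (all diagnoses pooled).**

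| 12-month mortality, curative/non-curative | Null rejection, unstratified | Power, unstratified | Power, stratified | Points lost |
|---|---|---|---|---|
| 10% / 20% | 5.0% | 55.5% | 56.7% | 1.2 |
| 5% / 30% | 3.9% | 60.4% | 64.5% | 4.1 |
| 3% / 40% | 3.4% | 67.1% | 73.4% | 6.3 |
| 2% / 60% | 1.1% | 77.7% | 88.2% | 10.5 |

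The stratified test rejects a true null about 5% of the time throughout. The loss depends on how far event rates differ.

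**Step 2. Sizes nearer to one diagnosis.** At 5%/40% and 60 to 150 per group, with continuum balanced between arms, the unstratified EC v. UC test rejects about 3% under the null, and stratifying adds about 5 to 8 points of power. Three-group tests show similar differences: 41% v. 47% at 150 per group (6 points), and 10–15% v. 16–23% at 50–75 per group (6 to 8 points).

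The balance condition matters. Diagnosis is not a randomisation stratum, so within one diagnosis the arms may match on continuum only approximately. Leaving the mix entirely to chance (46% non-curative on average, 4,000 runs, 60 to 150 per arm) brought unstratified null rejection back to about 5% and reduced the gain to about 2 to 5 points.

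**Step 3. Recurrence, EC v. UC, 150 curative + 200 survivors per arm, odds ratio 0.5, chi-square v. Cochran-Mantel-Haenszel.** Rates 10%/5%: 51.1% v. 51.4%. Rates 15%/3%: 54.7% v. 55.8%. Rates 25%/3%: 69.5% v. 72.3%. The loss is 0.3 to 2.8 points.

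**Step 4. Global three-group test, no true effect, Pre-I share shifted by 10 points.**

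- 300 per group, shifted towards non-curative: unstratified rejection 5.7% (10%/20%), 10.3% (5%/30%), 14.5% (3%/40%); stratified 4.7–5.5%.
- 60 per group, same direction: 4.1% (5%/30%) and 4.6% (3%/40%).
- 5%/40%, Pre-I with 10 points fewer non-curative: about 10% at 150 per group and 7–8% at 60–100 if the mix is sampled; 7% at 150 and 4–5% at 60–100 if it is held fixed. Stratified: 4–6%.

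**The case against.** The strongest reply is that little depends on these tests. SAP 9.3 calls them exploratory, splits them by diagnosis, adjusts its Cox and logistic models for continuum, and adds sensitivity adjustment if baseline differences appear. For recurrence and secondary cancers, adjusted global and pairwise comparisons are already planned. All of that stands, and it sets the severity. It does not supply a continuum-adjusted test for overall survival, nor say which test governs the binary endpoints.

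It can also be said that listing endpoints by continuum group means testing within each group. That reading is possible, but then the continuum covariate has no function.

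A reader might infer more than the documents support:

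- **That case mix can pass for an EC effect.** Randomisation is stratified by continuum, so case mix cannot systematically bias EC v. UC. The exposure is confined to the global test with Pre-I.
- **That the false-positive rate is high.** Rejection of 27–29% appears at 500 per group. Under the SAP target of about 1000 randomised, an arm has about 500 patients, of whom 60–70% (300–350) are curative or non-curative over all diagnoses. Even 150 in one diagnosis would be 43–50% of those.
- **That every endpoint is affected.** As SAP 9.3 lists them, disease-free and progression-free survival each concern one continuum group, so stratifying by continuum changes nothing. (SAP 2.0 lists progression-free survival for the curative group as well; the two lists should be reconciled.)
- **That continuum is a dominant prognostic factor.** The documents do not say so. SAP 9.3 attributes differing outcome rates to cancer type.

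**Conclusion.** The point holds in a limited form. The tests named in SAP 9.3 are unstratified, while continuum is both a randomisation stratum and a model covariate. If overall survival is pooled over continuum and mortality is 5% v. 40% with a hazard ratio of 0.60, the EC v. UC log-rank test is conservative (about 3%) and gives up about 5 to 8 points of power at 60 to 150 per group when the arms are balanced on continuum. The loss is smaller if balance within a diagnosis is only approximate. With rates as close as 10% v. 20% it is about 1 point. For recurrence it is 0 to 3 points.

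The global test with Pre-I rejects about 5% at 60 per group and about 10% at 150 under a 10-point shift; the range at 60 is 4% to 7%, according to how the mix is modelled. Stratifying restores about 5%, but the Pre-I comparison remains non-randomised. Every event rate, effect size and shift here is assumed. At per-diagnosis sizes, power is low with either test. Severity is minor: no confirmatory conclusion depends on these analyses.

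**What to change.** In SAP 9.3:

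1. State whether overall survival, recurrence and secondary cancers are tested within or across continuum groups.
2. If across, use a log-rank test stratified by cancer continuum for overall survival, or take the p-value from the continuum-adjusted Cox model already planned. As that model has Pre-I as referent, specify the EC v. UC contrast.
3. For recurrence and secondary cancers, use a Cochran-Mantel-Haenszel test stratified by continuum, or name the adjusted logistic comparisons as the governing test and keep the chi-square as descriptive.
4. Report the randomised EC v. UC comparison separately from any comparison that includes Pre-I.
5. Do not add cluster strata within a diagnosis where events are sparse.

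The cost is a few sentences in the SAP and one extra term in the test calls. No new data are needed, and SAP 1.0 says that changes to the SAP do not require a protocol amendment.
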